Postintervention care includes (1) partial weight-bearing for 1 month; (2) active strengthening of the muscles without overloading the knee using, if possible, the blood-flow restriction technique and gentle nonweight-bearing muscle activation, including core stability exercises; (3) mobility; and (4) modification of daily activities, work, and sports habits.

A total of 5 follow-up visits are planned for the study, during which principal and secondary outcomes will be gathered by a blinded investigator. At the 1-month and 2-month follow-up visits, patients in both study arms will receive 2 additional ultrasound-guided PRP injections performed by the blinded investigator and following the same Arthrex autologous conditioned plasma technique. The same postintervention care will be provided after these 2 PRP injections. Figure 1 shows the study flow chart.

Anticoagulants (eg, aspirin) and anti-inflammatory drugs (eg, ibuprofen, naproxen, meloxicam) should not be used 2 weeks before and 2 weeks after each injection as it can potentially interrupt the therapeutic acute inflammatory response and cytokine production.

Active physical therapies regimens, orthotics use, sports, and daily activities are adapted to the patient, on a day-by-day basis, during the postintervention care.

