### Outcome Measurements and Assessments

The primary outcome is functional improvement measured with the 0%-100% normalized WOMAC at the 6-month follow-up, where 0% indicates complete absence of symptoms and 100% indicates maximal possible symptom severity. A clinically relevant functional improvement is a difference of 9.1 points out of 100 points.

The secondary outcomes will be clinical and radiological parameters gathered at the 1-month, 2-month, 3-month, 6-month, and 12-month follow-ups. These include a 10-point pain visual analogue scale (VAS) during maximal physical activity performed by the patient according to manageable pain and clinical recommendations, the 0%-100% normalized WOMAC [2], length of time to return to work and sports in days, adverse events (AEs), and serious adverse events (SAEs). Pain will be assessed as an AE of interest, during the intervention and 48 hours following the intervention.

The improvement in cartilage quality will be assessed at the 6-month and 12-month follow-ups (previous MRI should not be dated more than 3 months before the intervention) using 3 key MRI-based scoring systems: Area Measurement and Depth and Underlying Structures (AMADEUS) [13], Whole-Organ Magnetic Resonance Imaging Score (WORMS) [22], and Magnetic Resonance Observation of Cartilage Repair Tissue (MOCART) [23].

We initially planned to statistically assess these outcomes at 6 months and 12 months. However, assessment of these parameters at other time points might be subject to exploratory analysis.

The participant timeline is presented in Table 1. The following information will be collected at baseline: age, gender, height, weight, BMI, smoking status, comorbidities, baseline Kellgren–Lawrence grade, current and previous treatments, and posttraumatic etiology. The set of clinical and radiological scores include the VAS, WOMAC, return to work and sports in days, AMADEUS, WORMS, and MOCART.

**Table 1 table1:** Study assessments and procedures at the study visits.

Procedures	Screening^a^	Baseline	Visit 1	Visit 2	Visit 3	Visit 4	Visit 5
Timing (visit window)	–3 weeks (+3 weeks)	0	1 month (±7 days)	2 months (±7 days)	3 months (±7 days)	6 months (±7 days)	12 months (±7 days)
Informed consent	X	—^b^	—	—	—	—	—
Inclusion/exclusion criteria	X	—	—	—	—	—	—
Baseline characteristics	—	X	—	—	—	—	—
Clinical scores	—	X	X	X	X	X	X
MRI^c^	—	X	—	—	—	X	X
Randomization	—	X	—	—	—	—	—
Lipoharvesting or sham lipoharvesting	—	X	—	—	—	—	—
Intervention^d^	—	X	—	—	—	—	—

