### Statistical Analysis

The WOMAC score will be normalized to a 0%-100% scale, where 0% indicates no symptoms and 100% represents the highest severity of symptoms. This normalization involves converting the raw scores into percentages, facilitating the interpretation and comparison of results across participants and study groups. The absolute difference at 6 months will serve as the primary outcome and will be compared using either the paired Student *t* test or the Wilcoxon signed-rank test, depending on the distribution of the variable, with intention-to-treat analysis. The absolute differences in secondary outcomes (changes from baseline to other time points) between the treatment and control groups will be evaluated with the appropriate statistical test (categorical variables: chi-square or Fisher exact tests; continuous variables: Student *t* or Wilcoxon rank tests). All analyses will include both intention-to-treat and per-protocol analyses. Effect estimates, 95% CIs, and descriptive *P* values will be reported whenever possible, along with corresponding graphs.

A post hoc analysis will attempt to identify variables of interest using the appropriate global linear model.

Since the intervention is considered low risk, no interim analysis is planned. In case of missing primary outcome data, patients will be withdrawn from the analysis. Patients missing secondary outcome data will remain in the study but be excluded from those specific analyses.

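### The primary analysis is called intention-to-treat but drops every patient without a 6-month WOMAC, so it is complete-case and leaves the earlier WOMAC scores unused

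*Protocol article*

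**What the plan says.** All references are to the protocol article.

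- **Endpoint** (Outcome Measurements and Assessments): "The primary outcome is functional improvement measured with the 0%-100% normalized WOMAC at the 6-month follow-up".
- **Analysis population** (Statistical Analysis): the primary test is chosen "depending on the distribution of the variable, with intention-to-treat analysis". A later sentence adds: "All analyses will include both intention-to-treat and per-protocol analyses".
- **Missing primary outcome** (same section): "In case of missing primary outcome data, patients will be withdrawn from the analysis".
- **Missing secondary outcome** (the next sentence): "Patients missing secondary outcome data will remain in the study but be excluded from those specific analyses".
- **Earlier scores** (Outcome Measurements and Assessments): "The secondary outcomes will be clinical and radiological parameters gathered at the 1-month, 2-month, 3-month, 6-month, and 12-month follow-ups". The list of these parameters includes "the 0%-100% normalized WOMAC [2], length of time to return to work and sports in days". Table 1 also schedules the clinical scores at baseline.

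The article describes no model, imputation or sensitivity analysis that would use the earlier WOMAC scores of a patient who has no 6-month score. The Sample Size section states no allowance for dropout.

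**The concern.** Whether a 6-month score exists is settled after randomisation and may depend on how the patient is doing. Excluding patients on that basis means the groups compared are no longer the groups randomised. The comparison is then protected only if the loss is unrelated to outcome, or at least distorts both arms equally. The article states no such assumption and keeps the intention-to-treat label.

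This is not a detail left to a statistical analysis plan. A rule is given, and it conflicts with the declared principle. It is also an avoidable loss: a patient who leaves after the 3-month visit would have WOMAC at baseline and at 1, 2 and 3 months, yet would contribute nothing to the primary result. At stake is bias in the only primary contrast and, to a smaller degree, precision.

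**Working it through.** **Inputs from the Sample Size section:** difference 9.1, SD of change 13.9, two-sided 5%, 54 per arm, stated power 90%. **Assumed, because the article gives no figures:** loss of 10% to 20% before 6 months, and a correlation of 0.5 to 0.7 between the 3-month and 6-month changes.

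**1. The plan's own figure.** Normal approximation: n per arm = 2 × (1.960 + 1.282)² × 13.9² / 9.1² = 49.03, so 50. The two-sample t test needs 50.01, so 51 per arm, 102 in total. The stated 108 is slightly more than its inputs require, and two-sample t power at 54 per arm is 0.921. The article does not explain the surplus. It is on the safe side, and nothing below depends on it.

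**2. Power when patients are removed from both arms** (two-sample t test):

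| Loss | n per arm | Power |
|---|---|---|
| 0% | 54 | 0.921 |
| 5% | 51.3 | 0.907 |
| 10% | 48.6 | 0.891 |
| 15% | 45.9 | 0.873 |
| 20% | 43.2 | 0.853 |

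Power drops below 90% once loss exceeds about 7%. If 15% are lost from one arm only (45.9 against 54), power is 0.898.

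**3. Bias in one arm, worst case.** Suppose the worst fraction p at 3 months all leave that arm. With jointly normal changes, the complete-case mean at 6 months shifts by r × SD × φ(z) / (1 − p), where z is the upper-p normal quantile. For p = 0.15, φ(z)/(1 − p) = 0.2332 / 0.85 = 0.274, and 0.7 × 13.9 × 0.274 = 2.67.

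| p | φ(z)/(1 − p) | Shift, r = 0.5 | Shift, r = 0.7 |
|---|---|---|---|
| 10% | 0.195 | 1.4 | 1.9 |
| 15% | 0.274 | 1.9 | 2.7 |
| 20% | 0.350 | 2.4 | 3.4 |

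The range of 1.4 to 3.4 points is 15% to 37% of 9.1. Milder inputs give less: 1.1 points at 5% loss with r = 0.7, and 0.8 points at 10% loss with r = 0.3.

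**4. Less extreme dropout, by simulation.** There were 54 patients per arm and 4,000 repetitions per scenario. The chance of leaving followed a logistic function of the 3-month change, and average loss over the two arms was 10% to 26%. The table shows the complete-case difference.

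| Who leaves | True difference 9.1 | No true difference |
|---|---|---|
| Poor responders, same mechanism in both arms | 8.5 to 8.7 | about 0 |
| Poor responders in the control arm; loss unrelated to response in the SVF arm | 7.4 to 8.3 | 0.8 to 1.7 |
| Poor responders in the control arm, good responders in the SVF arm | 4.8 to 7.1 | 1.5 to 3.4 |

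Predicting the missing 6-month change from the 3-month change within arm brought every scenario to within about 0.15 of the truth. This is expected, because dropout was made to depend only on the 3-month value. The direction reverses if poor responders leave the SVF arm instead.

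**The case against.** The strongest reply is that material bias needs dropout that differs by arm, and the design works against that. Both arms have incisions, a real or sham harvest, venipuncture, the same two later PRP injections and the same aftercare, and patients and outcome assessors are blinded. The Discussion also allows disclosure at 6 months, with access to SVF, when progress is unsatisfactory. That could give poor responders a reason to attend the 6-month visit. This stands: the documents do not show that differential dropout is likely. They do not rule it out either, since the same Discussion concedes that blinding may be breached if a patient questions the procedure.

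Three stronger readings are tempting, and the documents do not carry them.

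- **Adverse events are dropped.** A reader might infer this from the contrast between the two missing-data sentences: the one on secondary data limits the exclusion to the analyses concerned, and the one on the primary outcome has no such limit. But that sentence concerns missing primary data and may mean the primary analysis only. Adverse events are listed among the secondary outcomes, which are handled outcome by outcome, and Table 1 collects them at baseline and every follow-up visit. The text is ambiguous on this and says no more.
- **The early WOMAC scores are discarded altogether.** They are unused for the primary comparison. As secondary outcomes they may still be analysed.
- **The trial becomes underpowered.** Power with all 108 patients is 0.92, and 10% loss leaves 0.89, essentially the planned 90%.

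**Conclusion.** The point holds in a limited form. The plan attaches an intention-to-treat label to a complete-case analysis and does not use the scheduled 1-, 2- and 3-month WOMAC scores to protect the primary comparison. That rests on explicit text and needs no assumption.

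The size of the harm does need assumptions. The shift of about 1.4 to 3.4 points is a one-arm worst case under assumed loss and correlation. A reader might take its upper end as the expected bias, and nothing in the article supports that. With a common dropout mechanism, the false difference under no effect is about zero, and a true 9.1 is only mildly understated. The main issue is exposure to bias that the trial's own data could reduce; the loss of power is small.

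**What to change.** In Statistical Analysis, replace both the missing-data sentence for the primary outcome and the sentence naming the primary test. Changing only the first would leave the paired t test or signed-rank test standing as a second, conflicting primary analysis. Suggested content:

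- **Primary analysis:** all randomised patients, analysed as randomised, in a longitudinal model of WOMAC at baseline and at 1, 2, 3 and 6 months, adjusted for the stratification factors. The primary contrast is the between-group difference at 6 months. A mixed model for repeated measures with baseline as part of the outcome vector would do, because it also keeps patients who have only a baseline score. Multiple imputation from the earlier scores is an equally acceptable route.
- **Sensitivity analyses:** the complete-case comparison, and a delta-adjusted analysis for informative dropout.
- **Clarification:** a missing 6-month WOMAC does not remove a patient from secondary outcome or adverse event reporting.

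The cost is wording and slightly more analysis work, with no extra visits, patients or data. The primary model would rest on a missing-at-random assumption, which the delta-adjusted analysis is there to test. The change is easiest now: the Results section says this version is ready to go to the regulatory authorities, and the Ethics Review Approvals section requires ethics committee approval for changes once the protocol is approved.

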### Oversight and Monitoring

For quality control of the study conduct and data retrieval, all study sites will have regular monitoring activities performed by appropriately trained and qualified monitors, who are outsourced by the sponsor-investigator. Monitoring activities will consist of on-site monitoring as well as remote and centralized monitoring.

The objectives of a monitoring visit are to (1) verify the informed consent form process for each monitored participant, (2) verify the prompt and accurate recording of all monitored data points and prompt reporting of all safety events, (3) compare collected data with participants’ source documents, and (4) ensure investigators comply with the protocol.

The monitors may also inspect the clinical site regulatory files to ensure that regulatory requirements and applicable guidelines (International Council for Harmonisation [ICH] Good Clinical Practice [10]) are being followed.

SAEs will be defined as any untoward medical occurrence that results in death, is life-threatening, requires inpatient hospitalization or prolongation of existing hospitalization, results in persistent or significant disability or incapacity, or in a congenital anomaly or birth defect. SAEs should be followed until resolution or stabilization. Assessment of causality will be based on the criteria listed in the ICH E2A guidelines [10], and severity will be graded based on the Common Terminology Criteria for Adverse Events Version 5 [27]. All SAEs will be reported immediately and within a maximum of 24 hours to the sponsor-investigator of the study. The sponsor-investigator will re-evaluate the SAE and return the form to the co-investigator. SAEs resulting in death will be reported via the sponsor-investigator to the Swiss Business Administration System for Ethics Committees and to the other ethics committees involved in the trial within 7 days.

Regular audits are not planned. For the purpose of on-site inspection or audit, the competent authorities or ethics committee may require access to all source documents and other study-related records. The sponsor-investigator and local investigators must ensure the availability of these documents at any time.

### Ethical Considerations

#### Ethics Review Approvals

To comply with local regulations in Switzerland regarding clinical trials involving human subjects, this study design is classified as risk category C [28-30].

Therefore, both Swissmedic (the Swiss authority responsible for the authorization and supervision of therapeutic products) and the local ethics committee must review and approve the research protocol. Since both applications require a significant investment, a grant request will be submitted prior to applying to these two institutions. The principal investigator will obtain approval from the competent authority (Swissmedic) before the start of the study. Once the protocol is approved, no changes will be made without prior approval from the ethics committee, except when necessary to eliminate immediate hazards to participants.

#### Informed Consent

The recruiting investigator will explain the study's nature, purpose, procedures, duration, risks, benefits, and discomforts. Participation will be voluntary, and participants can withdraw at any time without affecting their medical care. Each participant will receive an information sheet and consent form to make an informed decision, with time to consult others and ask questions. Consent will be obtained before any procedures, and the signed form will be kept as part of the records. Participants will be informed that authorized individuals may examine their medical records. The informed consent is available in Multimedia Appendix 5.

#### Privacy and Confidentiality

The investigator upholds the participant's right to privacy and complies with privacy laws, ensuring anonymity in scientific presentations and publications. Medical information from the study is confidential, and third-party disclosure is prohibited. Participant confidentiality will be maintained using identification code numbers. Authorized representatives, such as those from Swissmedic or the ethics committee, may access relevant medical records for data verification.

#### Compensation Details

There is no compensation provided for participants in this human subjects research.

#### Identifiable Features

Identifiable features of research participants in any image or supplementary material will not be visible.

## Results

This version of the study protocol presented in this article is ready to be presented to the Switzerland regulatory authorities. A request for funding was submitted to the Swiss Medical Foundation in December 2024, and the study was registered in the portal for clinical trials in Switzerland (number pending).

Enrollment to the study is expected to begin in July 2025 and finish in July 2027. Final end points will be gathered in August 2027, and the results are expected to be published in late 2027. The findings will be shared through conference presentations targeting rehabilitation and sports medicine specialists. The Swiss Medical Network and Switzerland's Physical Medicine and Rehabilitation Network will be engaged through presentations at their yearly research events to help implement findings in clinical settings.

Given the open-access nature of the target journal, all results will be publicly available. To gather feedback, we will use postpublication surveys, interactive webinars, and follow-up interviews with patients and practitioners to discuss the applicability and impact of SVF therapy in practice.

## Discussion

This study design intends to assess the potential benefits of SVF injection, an easy-to-use, simple, and noninvasive cellular therapy, on the most frequent joint disease. With this high-quality RCT, SVF will be compared with one of the most commonly used noninvasive therapies in the field of sports medicine, PRP.

Based on available clinical trials, we hypothesize that SVF treatment in addition to PRP may lead to significant clinical and radiological improvement in patients with knee osteoarthritis. The WOMAC and VAS scores are among the most commonly used clinical outcomes in RCTs and meta-analyses for knee osteoarthritis research. For radiological assessment, 3 MRI-based scoring systems—AMADEUS, MOCART, and WORMS—are frequently cited in RCTs. Including these scores as primary and secondary outcomes will facilitate future meta-analyses and allow direct comparison of our trial’s results with those of previous studies

Compared with PRP, cellular therapy with SVF requires more physician training, takes more time, and ultimately incurs higher costs. In other words, it demands greater resources. From the authors’ perspective, patients and caregivers should only invest in these additional resources if clear benefits are demonstrated, which this study aims to establish.

Different techniques have been used to inject or implant cellular therapy with MSCs to the required site, but consensus about the best approach does not exist. However, biologically, some elements support the use of AD-MSCs for nonbone tissue. AD-MSCs would theoretically be more resilient than B-MSCs to the hypoxic articular cavity because they are less dependent on mitochondrial respiration for energy production. From an immunological perspective, AD-MSCs should be preferable to B-MSCs since B-MSCs could induce a higher immunological response due to their higher cell-surface human leukocyte antigen class I expression. AD-MSC highly expresses interleukin-33, which promotes regulatory T cell phenotype proliferation, which would theoretically mean a beneficial effect on anti-inflammatory responses [14].

Han et al [11] compared AD-MSC with B-MSC for knee osteoarthritis and found a superior therapeutic effect of AD-MSC compared with B-MSC on VAS and WOMAC scores. Zhou et al [31] performed a meta-analysis comparing AD-MSC and B-MSC therapies, and they found no statistical differences in clinical scores between the two therapies but did find a higher variability in B-MSC results, suggesting AD-MSCs might be a more reliable therapeutic option. Ude et al [32] found better chondrogenic inductions and gene expressions with AD-MSCs than with B-MSCs.

The therapeutic potential of MSCs is of great interest due to their possible long-term chondroprotective and even chondroregenerative effects. A meta-analysis by Lee et al [19] demonstrated significant improvements in imaging outcomes measured using the WORMS and MOCART scores. WORMS scores improved significantly with SVF therapy compared with controls at both 6 months and 12 months posttreatment (6 months: mean difference [MD]=–18.29, 95% CI – 21.75 to –14.84; 12 months: MD=–26.78, 95% CI –29.95 to –23.61). Similarly, MOCART scores showed notable improvements with AD-MSC therapy at 6 months (MD=24.7, 95% CI 5.92 to 43.48) and 24 months (MD=25.8, 95% CI 5.52 to 46.08), while SVF therapy resulted in significant gains at 6 months, 12 months, and 24 months (6 months: MD=30.11, 95% CI 26.08 to 34.13; 12 months: MD=36.82, 95% CI 23.95 to 49.68; 24 months: MD=10.60, 95% CI 1.37 to 19.83).

The comparative superiority of SVF over AD-MSCs, or vice versa, remains uncertain, as no RCT has yet directly addressed this question. An observational study [33] suggested the superiority of AD-MSCs, but further evidence is needed.

The meta-analysis by Lee et al [19] showed some differences between both therapies on clinical outcomes. A significant improvement in the VAS score was found at 6 months and 12 months with AD-MSCs (6 months: MD=–1.62, 95% CI –2.46 to –0.79; 12 months: MD=–1.97, 95% CI –3.22 to –0.72), whereas SVF showed significant results only at 12 months (6 months: MD=–2.32, 95% CI –5.15 to 0.52; 12 months: MD=–2.13, 95% CI –3.06 to –1.21). In contrast, functionality measured with WOMAC scores improved significantly 6 months after SVF treatment (MD=–6.12, 95% CI –10.71 to 1.52), while AD-MSC therapy yielded significant improvements only after 12 months (6 months: MD=–1.96, 95% CI –5.36 to 1.45). At 12 months and 24 months, both SVF and AD-MSC therapies produced significant improvements in the WOMAC score (12 months SVF: MD=–9.09, 95% CI –12.67 to –5.51; 12 months AD-MSC: MD=–9.19, 95% CI –12.48 to –5.90; 24 months SVF: MD=–10.71, 95% CI –18.49 to –2.93; 24 months AD-MSC: MD=–6.88, 95% CI –10.24 to –3.52).

The first main strength of our study design is the large sample size. Second, our study population is well-designed and reproducible, with standardized diagnostic criteria and failure of a first-line standardized rehabilitation plan. Third, the multicenter design allows for better reproducibility of patient selection and management, even if interventions are performed at the main study center by a single investigator. This is, however, a study strength, as it will avoid bias related to the intervention techniques.

A sham lipoaspiration procedure with the patient awake is performed to maintain blinding in the control group. Despite all precautions taken to uphold allocation concealment, breaches may occur if the patient diligently questions the procedure. For ethical reasons, if at 6 months, the progression is unsatisfactory, the intervention's nature may be disclosed if deemed clinically relevant, allowing the patient to benefit from SVF infiltration. Consequently, the study may be limited, as the initial 12-month secondary outcomes will not be considered in the final analysis. Finally, the patient selection, clinical follow-up, and rehabilitation plan might differ across the various recruitment centers (multicenter design).

The minimal clinically important difference was chosen as the limit to detect a clinically relevant difference for sample size calculation. From the authors’ point of view, even in the case of statistically significant positive effects of the treatment, the generalization of the procedure should be balanced by a complementary cost-effectiveness analysis. Indeed, in case of mild benefits, other procedures such as strengthening, biomechanics adaptation, medication, annual PRP infiltrations, shockwave therapies, or even slight daily activity adaptations might be options of choice. One should be aware that cellular therapies should not be presented to patients as a “magic potion” or “youth elixir.” Especially, the authors warn about the recognized risk of financial benefits based on overemphasized clinical promises.

This study will contribute data to establish the clinical relevance of SVF treatment for the most relevant disease of the musculoskeletal system.

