### Randomization and Blinding

Study participants will be randomized at a 1:1 ratio to either the intervention arm or the active comparator arm using a randomization table and blocked randomization with blocks of 4 patients. Participants will be assigned to specific strata based on age (older or younger than 40 years) and the presence of cartilage defects (partial, full, or full with bone deformation).

The unblinded investigator responsible for the study interventions will perform the randomization shortly before administering the interventions. This study is triple-blinded: (1) Participants will be unaware of their group assignment throughout the intervention and study duration, (2) the investigator performing the intraarticular injection and the outcome assessor will remain blinded, and (3) the statistician will also be blinded. The investigator responsible for preparing the PRP+SVF or PRP-only preparation will be unblinded and will not participate in outcome assessments.

All patients will undergo a venipuncture, either a lipoaspirate or a sham lipoaspirate, followed by an ultrasonographically guided PRP or PRP+SVF injection. It is anticipated that unblinding will not be required to ensure patient safety, as no known adverse effects of the SVF (such as local pain, tenderness, hematoma on donor site, or infection) require unblinding for clinical management. However, if unblinding becomes necessary due to unexpected circumstances, the unblinded investigator will disclose the allocated intervention for the affected patients.

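### The Discussion drops 12-month outcomes after a foreseen 6-month disclosure, which conflicts with the Methods; its scope is unclear, and either reading damages the 12-month results

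*Protocol article*

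**What the plan says.** The Discussion, in its paragraph on limitations, says that "if at 6 months, the progression is unsatisfactory, the intervention's nature may be disclosed if deemed clinically relevant", with the purpose of "allowing the patient to benefit from SVF infiltration". It draws the consequence that "the study may be limited, as the initial 12-month secondary outcomes will not be considered in the final analysis". It gives no threshold for unsatisfactory progress, does not say whether disclosure must wait for the 6-month assessments, and does not say whether the exclusion covers disclosed patients or everyone.

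The Methods say otherwise:

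- Randomization and Blinding: "Participants will be unaware of their group assignment throughout the intervention and study duration". The same section says "It is anticipated that unblinding will not be required to ensure patient safety", and the one exception it allows is that "if unblinding becomes necessary due to unexpected circumstances, the unblinded investigator will disclose the allocated intervention for the affected patients".
- Outcome Measurements and Assessments: "We initially planned to statistically assess these outcomes at 6 months and 12 months". The next sentence leaves only other time points to exploratory work. Table 1 schedules clinical scores and MRI at both 6 and 12 months, and Study Design and the Abstract also list 12-month endpoints.
- Statistical Analysis: every analysis is to be done by intention-to-treat and per protocol. Patients without a secondary outcome leave that particular analysis. Disclosure and later SVF are not mentioned.

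**The concern.** The Discussion sentence is a data-handling rule, and it stands in a document whose Methods point the other way. A statistician given both cannot tell whether a 12-month comparison will be made, or in whom.

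Under either reading something is lost. Dropping all 12-month data removes the 12-month WOMAC, pain and return-to-activity results and the second of the two post-treatment MRI assessments, although all are scheduled. Dropping only disclosed patients makes inclusion at 12 months depend on how the patient was doing at 6 months. Randomisation no longer protects such a comparison, and it is not intention-to-treat. Patients allocated to PRP alone are the natural candidates for SVF, because the other arm has already had it. The loss would therefore probably fall more heavily on the control arm and take out its poorer responders, which would understate any SVF benefit. That imbalance is an inference; the protocol does not state it.

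**Working it through.** **1. The sections side by side**

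| Topic | Methods | Discussion |
|---|---|---|
| Participant blinding | Whole study; exception for unexpected circumstances | Disclosure foreseen at 6 months for unsatisfactory progress |
| 12-month outcomes | Scheduled and planned for analysis | Not considered in the final analysis |
| Analysis set | Intention-to-treat and per protocol for all analyses | Exclusion that follows from the 6-month result |

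A disclosure written into the protocol in advance is not an unexpected circumstance, so the exception does not remove the conflict.

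**2. Inputs for the disclosed-patients-only reading**

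From the protocol (Sample Size): SD of change 13.9, target difference 9.1, mean change −11.6 in the source study (used here as the control mean), 54 per arm. The protocol gives no 12-month power or bias figure to reproduce. Its sample size concerns the 6-month outcome and plays no part in this point beyond supplying these values.

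Assumed, because the protocol is silent: the 6-to-12-month correlation r, the fraction p removed, and the arm from which patients are removed.

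**3. Shift in the PRP mean if the worst fraction p at 6 months is removed from that arm only**

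Shift = r × SD × φ(z_p)/(1 − p), where φ is the standard normal density and z_p the normal quantile of p.

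- p = 0.20: φ = 0.280, and 0.280/0.80 = 0.350. With r = 0.5, 0.5 × 13.9 × 0.350 = 2.4; with r = 0.7, 3.4.
- p = 0.30: φ = 0.348, and 0.348/0.70 = 0.497. With r = 0.5, 0.5 × 13.9 × 0.497 = 3.5; with r = 0.7, 4.8.

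The range of 2.4 to 4.8 is 27% to 53% of 9.1. The shift makes PRP look better.

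**4. Simulation that includes removal in both arms**

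The simulation used 54 per arm and 4,000 trials per scenario. Unsatisfactory was taken to mean improvement of less than 9.1 points, with half or all of such patients dropped at 12 months. That rule makes about 43% of controls eligible and, with a true effect of 9.1, about 20% of the SVF arm. Positive differences favour SVF.

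| Dropped from | True difference | r | Estimate, half dropped | Estimate, all dropped |
|---|---|---|---|---|
| PRP only | 9.1 | 0.5 | 7.5 | 4.4 |
| PRP only | 9.1 | 0.7 | 6.7 | 2.4 |
| Both arms | 9.1 | 0.5 | 8.4 | 6.8 |
| Both arms | 9.1 | 0.7 | 8.2 | 5.8 |
| PRP only | 0 | 0.5 | −1.8 | −4.8 |
| PRP only | 0 | 0.7 | −2.5 | −6.7 |
| Both arms | 0 | 0.5 or 0.7 | about 0 | about 0 |

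With no true difference, the two-sided rejection rate is 11% to 60% for PRP-only removal and about 5% for removal in both arms.

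**5. Two alternatives in the same scenarios**

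- Using the 6-month value to inform the missing 12-month value recovers 9.1 to 9.2 when the truth is 9.1, and about 0 when it is 0. This is expected, because removal in the simulation depends only on the 6-month value.
- Keeping everyone as randomised holds the error rate at about 5%. If crossed-over controls gain the full 9.1 points, it estimates 5.2 to 7.3 when the truth is 9.1. As a check, with all eligible controls crossing over, 9.1 − 0.43 × 9.1 = 5.2.

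**The case against.** Several objections have force.

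- The sentence does not limit the exclusion to disclosed patients. Read literally, there is no 12-month comparison, so nothing is biased. This stands: a reader might infer that the plan certainly produces a biased 12-month contrast, but the text supports that only under one of its two readings. The other reading contradicts the Methods instead.
- The trigger is poor progress, not allocation, so SVF patients may be disclosed too. This also stands. PRP-only removal is the unfavourable case; removal in both arms does less harm and, with no treatment effect, essentially none.
- A reader might infer that the tissue-regeneration objective is lost. It is not: MRI is also scored at 6 months, and that comparison survives if completed before disclosure.
- The primary outcome is at 6 months, P values are described as descriptive, and the likely bias runs against SVF, so a false claim of superiority is not the main danger. This bears on severity, and it is why the point ranks below those touching the primary analysis.
- The authors acknowledge the matter as a limitation. That is candid, but it does not make the sections agree.
- An unseen analysis plan might settle the handling. It might, but the point is a rule that the protocol states and its own Methods contradict, not a missing detail.

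**Conclusion.** The conflict is established from the text: a foreseen disclosure against blinding for the study duration, and an exclusion of 12-month outcomes against planned 12-month endpoints and intention-to-treat for all analyses. The scope of the exclusion is ambiguous, and both readings are defects.

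The size is not established. Only the SD, the target difference, the source-study mean change and the arm size come from the protocol. The correlation, the fraction removed, the threshold and the arm affected are assumptions. The figure of 2.4 to 4.8 points illustrates what outcome-dependent removal from one arm can do; it does not predict what will happen in this trial.

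Two stronger conclusions may tempt a reader and are not supported. The 6-month primary result is not compromised if its assessment precedes disclosure, although the protocol should say that it does. Nor are the 12-month data bound to be uninterpretable, because that depends on the scope of the rule and on how many patients are disclosed in each arm. The point should be fixed, at a severity suited to secondary outcomes.

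**What to change.** Whether and when allocation is disclosed or SVF offered is for the sponsor to decide, and no view is taken here. The sections on outcomes, blinding, statistical analysis and the Discussion must be made to agree with that decision. On the data side:

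1. State that the 6-month WOMAC and MRI are completed and recorded before any disclosure.
2. Delete the sentence that leaves 12-month outcomes out of the final analysis.
3. Keep the 12-month collection already scheduled in Table 1 for everyone, including disclosed patients.
4. Analyse 12 months in all randomised patients as randomised. Beside it, fit a mixed model in which values after open-label SVF are set to missing and earlier visits inform them. State in advance which of the two is the main 12-month estimand; either order is defensible.
5. Report disclosures and open-label SVF by arm.

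The cost is protocol wording and one further analysis, with no extra visits. The as-randomised estimate is diluted by crossover, possibly substantially (5.2 to 7.3 against a true 9.1 in the scenarios above). The mixed model relies on earlier visits explaining who received SVF. For these reasons both results should be shown.
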